**Figure 2 Fig2:**
[figure not shown]
**Repeat creatinine test schedule.**

**Table 1 Tab1:** **Study timeline**

	**Study period**							
	**Enrolment**	**Allocation**	**Post allocation**					**Close-out**
	**-t** _**1**_	**o**	**Day** _**1**_	**Day** _**2**_	**Day** _**3**_	**Day** _**4**_	**etc.**	**Day** _**28**_
Enrolment:								
Eligibility screen	X							
Informed consent	X							
Demographic data collection	X							
Medication use data collection	X							
serum creatinine testing	X				X			X
Allocation		X						
Interventions:								
Intravenous saline solution			X					
Oral salt water			X					
Assessments:								
Adherence to intervention			X					X
Adverse events			X					
serum creatinine testing					X			X

### Outcomes

Feasibility of conducting the definitive trial is the primary outcome for this pilot study. It will be determined by the proportion of patients who will 1) consent to enrolment in the study (recruitment rate), 2) complete the fluid ingestion at dose required in both arms (adherence to intervention), and 3) complete repeat measures of creatinine at 48 hours and 28 days (follow-up). Additionally, we will identify logistical issues related to screening, protocol implementation, randomization implementation strategy, time, and budget problems that can occur during the definitive trial.

The secondary outcome for this pilot trial is safety. It will be assessed by adverse effects occurring after receiving the trial treatment. Adverse effects that may occur because of the ingestion of water and salt include: nausea or gastrointestinal symptoms. Symptoms that may occur because of the saline solution or the technique of administration include discomfort with the venipuncture at the site of injection such as skin irritation and pain, hemorrhage, hematoma, thrombosis, phlebitis. All adverse events effects will be assessed by patients self-reported symptoms using a questionnaire with these symptoms listed and will be recorded in a Case Report Form at the end of the volume expansion protocol.

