### Criteria

#### Inclusion criteria

Chronic kidney disease (as defined by a glomerular filtration rate (GFR) < 30 mL/min/1.73 m^2^ using the Chronic Kidney Diseases (CKD)-EPI formula calculated on the day of screening [38];Undergoing an outpatient intravenous contrast-enhanced CT of the chest or abdomen;Age ≥ 18 years

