### Data collection

At baseline, participant demographic information (including ethnicity, sex, month and year of birth), CT scan characteristics, medical history and medication use will be recorded. On the day of the CT scan, before oral or IV fluids are given, a SCr will be measured that will be considered as the baseline value. A subsequent SCr level will be measured at 48 hours post-CT. If the SCr at 48 hours has increased by ≥25% or ≥44 μmol above the baseline value, the SCr will be repeated every 48 hours until it returns to within 25% of baseline or < 44 μmol above baseline or the patient needs to initiate acute dialysis. If the SCr has not returned to within 25% of baseline or < 44 μmol above baseline by day 14 post-CT, the SCr will be measured again on day 21. All participants (regardless of whether they developed AKI) will have SCr repeated on day 28 post- CT (Figure 2). The SCr will be measured in the biochemistry lab at the Ottawa Hospital. The repeat creatinine measurements, though underpowered for any assessment of efficacy, will allow us to ascertain the proportion of patients who follow-up at each time point, which will be critical for our larger definitive trial. The study timeline is shown in Table 1.

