#### Safety

For the safety outcome, we will calculate the frequency of overall adverse events that will occur in each trial arm and we will compare them using an unadjusted chi-square test or Fisher’s exact test. Univariate descriptive statistics including measures of central tendency and dispersion will be used to report the frequency of adverse events. This outcome will be underpowered to draw any definite conclusions, but will be conducted to help us design the definitive trial.

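### Site complaints are linked to saline and read once, although both arms have venous access that day: arm-level rates are inflated and the between-arm difference is diluted

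*Protocol article*

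**What the plan says.** Safety is the secondary outcome, defined under Outcomes as adverse effects that occur after the trial treatment is received. That section sorts the expected symptoms by route. For the oral arm: "Adverse effects that may occur because of the ingestion of water and salt include: nausea or gastrointestinal symptoms". For the intravenous arm: "Symptoms that may occur because of the saline solution or the technique of administration include discomfort with the venipuncture at the site of injection", with skin irritation, pain, hemorrhage, hematoma, thrombosis and phlebitis as the further items. All are "assessed by patients self-reported symptoms using a questionnaire with these symptoms listed", and the result "will be recorded in a Case Report Form at the end of the volume expansion protocol".

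Two other sections bear on this. An inclusion criterion that applies whatever the arm reads "Undergoing an outpatient intravenous contrast-enhanced CT of the chest or abdomen". Data collection adds: "On the day of the CT scan, before oral or IV fluids are given, a SCr will be measured". The Outcomes section mentions neither exposure.

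The analysis under Safety is by randomized arm: "we will calculate the frequency of overall adverse events that will occur in each trial arm and we will compare them", with an unadjusted chi-square or Fisher's exact test. The same paragraph concedes: "This outcome will be underpowered to draw any definite conclusions". The Discussion nevertheless gives the results a use: the frequency and severity of adverse events will inform the judgement on whether a larger trial's benefits outweigh its risks.

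**The concern.** The symptoms listed for saline are symptoms of having a vein punctured, and on the CT day that happens to everyone. An oral-arm patient with a sore contrast cannula or a bruise from the blood draw reports the same item as an intravenous-arm patient with trouble at the saline line. The only recording time described comes after all these punctures. Nausea present before the first capsule raises a similar problem for the gastrointestinal items: the definition of the outcome excludes it, but a single reading at the end gives no means of telling it apart.

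Two results are affected. The between-arm difference shrinks, because a patient who already has a complaint from a shared cause cannot add a second one to a yes/no count. And each arm's frequency, read alone, overstates what that route does to patients. The second effect matters more here, because rates from the pilot are to be carried into the decision on the definitive trial.

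**Working it through.** **Inputs from the article.** 50 patients in total (Participants), so about 25 per arm if allocation is equal, as in the block example under Randomization and allocation concealment. Contrast access in both arms (Inclusion criteria). A pre-fluid creatinine sample on the CT day in both arms (Data collection). Table 1, as it can be read here, marks no creatinine on that day, but contrast access alone is enough for the premise. One end-of-protocol recording (Outcomes). Frequencies compared by arm (Safety).

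**Inputs that are assumptions.** The article gives no complaint rates and no significance level. Let b be the risk of a site complaint from the shared punctures and r the added, independent risk from the saline infusion. Tests are taken at two-sided 0.05.

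**Formulas.** Oral arm: p(oral) = b. Intravenous arm: p(IV) = 1 − (1 − b)(1 − r). Difference = r(1 − b). Share of intravenous-arm complaints added by the infusion = r(1 − b) / p(IV).

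**One case, b = 0.20 and r = 0.15.**
- p(IV) = 1 − 0.80 × 0.85 = 0.32, or 8 of 25.
- p(oral) = 0.20, or 5 of 25 with no saline infusion at all.
- Difference = 0.32 − 0.20 = 0.12, against 0.15 with no background.
- Share added by the infusion = 0.12 / 0.32 = 37.5%.

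**Range, r = 0.20, 25 per arm, power of Fisher's exact test by full enumeration.**

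| b | p(IV) | Difference | Share added by infusion | Power |
|---|---|---|---|---|
| 0 | 0.20 | 0.20 | 100% | 38% |
| 0.10 | 0.28 | 0.18 | 64% | 25% |
| 0.20 | 0.36 | 0.16 | 44% | 15% |
| 0.30 | 0.44 | 0.14 | 32% | 12% |
| 0.40 | 0.52 | 0.12 | 23% | 10% |

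With r = 0.30 the difference falls from 0.30 to 0.18 and power from 81% to 20% over the same range of b. With r = 0.10 power is 3 to 7% throughout.

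**Reading.** The difference is positive whenever r > 0 and zero when r = 0, so the comparison keeps its meaning. The share column falls much faster than the difference, so the raw intravenous-arm rate is the figure most easily misread.

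**Pooling the symptom types.** Take b = 0.20 in both arms, saline adding site complaints with risk 0.15, and oral salt adding gastrointestinal complaints with risk 0.15 (all assumed). The proportion with any complaint is then 1 − 0.80 × 0.85 = 0.32 in each arm, a difference of zero although each route has its own harm. An overall frequency alone can hide this.

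**The case against.** A reader might infer that site complaints cannot be attributed to the route at all. The documents do not support that. Allocation is randomized, the shared punctures fall on both arms, and the Safety section compares the arms. The oral arm supplies the background rate, and subtracting it is the purpose of a control group. What cannot be attributed is a single event, or one arm's rate taken alone.

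A reader might also infer that the questionnaire itself assigns these symptoms to saline. The article does not show that either. The linking sentence speaks of what may occur and explains which symptoms are listed. One list is described, with no version by arm and no rule for attribution. The form itself is not shown, so it may already carry a site item, and the absence of one from a journal article is not a finding. What the article does fix is the time of recording, and it describes only one.

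It can fairly be said that the dilution is small. In the worked case it is 3 points, or 0.03 × 25 = 0.75 of a patient, well inside sampling error. That stands, and it keeps the point minor. It does not help the arm-level rates, which a larger sample would not correct.

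The outcome definition also excludes symptoms that began before treatment. That is right in principle, but a pre-fluid reading is what would make it workable. Complaints from contrast access would remain in any case.

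Finally, a remedy that counted only events judged to come from saline would set the oral arm's site count to zero by construction and replace a randomized comparison with causal judgement in a trial that is not blinded. That objection is sound, and the fix below avoids it.

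**Conclusion.** The point holds in a limited form. The protocol links venous complaints to saline without noting that both arms have venous access that day, and it describes a single recording at the end. The between-arm difference still identifies the effect of the route, but it shrinks by the factor (1 − b). The arm-level frequencies include complaints that the study fluid did not cause, and these frequencies feed the judgement on the larger trial.

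The size is unknown because the article gives no rates. With an assumed added risk of 0.20 and background from 0 to 0.40, the difference runs from 0.20 down to 0.12, and the infusion's share of intravenous-arm complaints from 100% down to 23%. These figures assume independent risks, equal background in the two arms and 25 patients per arm.

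Equal background is itself open to question. Volume expansion ends 2 hours after the CT in the oral arm and 6 hours after it in the intravenous arm, so a contrast-site complaint has longer to appear before the intravenous-arm form is completed. Self-report is also unblinded. Neither effect is sized here.

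Severity is minor: safety is a secondary outcome in a pilot that declares this comparison underpowered.

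**What to change.** - Give the same symptom form in both arms twice on the CT day: just before study fluids start, after the blood draw, and again at the end of volume expansion. Count symptoms that are new or worse at the second reading.
- For each site symptom record the source (blood draw, contrast access, saline line, or one cannula used for both) as description only.
- Keep all new or worse events in both arms in the between-arm comparison. Do not restrict it to events judged to come from saline.
- Report site symptoms and gastrointestinal symptoms separately by arm, alongside the overall frequency already planned.
- State that the between-arm difference, not one arm's raw rate, is to be interpreted and carried into planning of the definitive trial.

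The cost is a few minutes per patient and no extra visit. The pre-fluid reading removes existing nausea and blood-draw complaints from the count. It does not remove complaints from contrast access that arise later, and the source stays uncertain when one cannula serves both purposes.

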### Exclusion criteria

Inability to give informed consent;Previously enrolled in this study;Any contrast-enhanced test in previous 14 days (to exclude patients who might have ongoing AKI from previous contrast exposure);Congestive heart failure defined as NYHA class III or worse [39];Uncontrolled hypertension defined as SBP greater than 180 mm Hg or DBP greater than 110 mm Hg at screening;Currently receiving dialysis treatments.The physician ordering the CT scan has specifically ordered intravenous saline, sodium bicarbonate or n-acetyl cysteine.Scheduled to receive oral contrast solution as part of CT scan procedure

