### Trial intervention and dosing

#### The oral salt and water arm

Participants randomized to this arm of the trial will receive 0.1 g/kg of salt (NaCl) in capsule form and 12 mL/kg of water. Patients weighing more than 110 kg will receive the same amount as per a 110 kg patient [18]. This dosage was based on the trial of Dussol et al. in which oral salt was given using a pre-specified, weight-based approach [32]. This trial showed that 50% more oral salt ingestion, compared to intravenous saline, produced equivalent urinary sodium excretion. We have used these proportions to formulate the equivalent oral salt dosing. The oral water dosing has been calculated to make the overall composition approximately isotonic similar to the intravenous saline arm. One third of the oral salt and water will be given in 1 hour before the CT and 2/3 in the 2 hours post-CT. Specifically, 0.03 g/kg of NaCl and 4 mL/kg of water in the one hour before CT and 0.07 g/kg of NaCl and 8 mL/kg of water taken over 2 hours post-CT. The salt capsule and water will be taken in presence of the research personnel who will record on an assessment form that the patient has received the intervention (ingested the oral salt and water).

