## Discussion

The proposed project is a pilot trial of a simple pragmatic intervention (oral salt and water) in comparison to the standard of care (intravenous saline) for prevention of acute kidney injury after IV contrast administration. The results of our pilot study will provide crucial data to the planning of a large multicentre randomized trial to determine if oral salt and water administration is as effective as intravenous saline in the prevention of radiocontrast-induced AKI occurring after an IV contrast administration. For this definitive trial, we will study efficacy (incidence of AKI) as primary outcomes, with secondary outcomes including clinical (hospitalization, need for dialysis, and mortality) and health services aspects (economic analysis). A lower recruitment rate in the pilot trial will help us to plan adding more sites or a longer recruitment period for the definitive trial. Protocol adherence and follow-up measurements will provide additional feasibility information to plan refinement of the final protocol as well as adjust sample size estimates for a larger trial. Knowledge of the frequency and severity of the adverse events will be used by the trial management group to determine if the potential benefits of conducting a larger trial outweigh the potential risks with the proposed intervention in a larger trial.

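### As described, the safety questionnaire names no symptom of the sodium and volume load that both arms give, and no severity grade is described although the plan relies on severity

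*Protocol article*

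**What the plan says.** Safety is the secondary outcome. The Outcomes section names the expected effects by route. For the oral arm: "Adverse effects that may occur because of the ingestion of water and salt include: nausea or gastrointestinal symptoms". For the intravenous arm: "discomfort with the venipuncture at the site of injection such as skin irritation and pain, hemorrhage, hematoma, thrombosis, phlebitis". All adverse events are then said to be captured in one way. They "will be assessed by patients self-reported symptoms using a questionnaire with these symptoms listed", and the result "will be recorded in a Case Report Form at the end of the volume expansion protocol". Table 1 marks adverse events on Day 1 only. The Data collection section and Table 1 schedule creatinine after dosing, but no blood pressure.

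The population is defined by "Chronic kidney disease (as defined by a glomerular filtration rate (GFR) < 30 mL/min/1.73 m". The Exclusion criteria remove "Congestive heart failure defined as NYHA class III or worse" and patients with systolic pressure above 180 or diastolic above 110 mm Hg at screening. The oral arm receives "0.1 g/kg of salt (NaCl) in capsule form and 12 mL/kg of water". The intravenous arm receives 0.9% saline, 3 mL/kg in the hour before CT and 1 mL/kg/hour for 6 hours after it.

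The Safety analysis compares the overall frequency of adverse events between arms. The Discussion states the purpose: "Knowledge of the frequency and severity of the adverse events will be used by the trial management group" when it weighs the benefits of a larger trial against its risks. Under Study management and patient safety, the DSMB monitors adverse events throughout and reviews all serious ones.

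**The concern.** Every symptom the protocol names belongs to a route of administration: the stomach for one arm, the needle site for the other. The exposure common to both arms is the sodium and volume load itself, and the patients have advanced kidney disease. The Background reports that oral sodium and water loading raises cardiac output quickly, so the authors regard the load as physiologically active. Yet no named item would prompt a patient to report breathlessness or swelling. A rise in blood pressure cannot be self-reported, and no reading is scheduled that would show it.

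Two things are at stake. First, a report of no load-related safety signal could mean only that nobody asked. The overall event count would then compare stomach complaints in one arm with cannula complaints in the other, and would miss the effect that can be compared between arms on the same item. Second, the Discussion draws on severity, but the methods describe neither a severity measure nor an analysis of one.

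**Working it through.** The plan states no figure on this point, and it says that no formal sample size calculation was done. The check is therefore a comparison of sections, with supporting arithmetic.

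**1. What is captured, against what is given**

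| Element | Where | Content |
|---|---|---|
| Symptoms named, oral arm | Outcomes | Nausea or gastrointestinal |
| Symptoms named, intravenous arm | Outcomes | Venipuncture-site effects |
| Method | Outcomes | Self-report on a questionnaire listing these symptoms |
| Timing | Outcomes; Table 1 | End of volume expansion; Day 1 |
| Blood pressure after dosing | Data collection; Table 1 | Not scheduled |
| Severity | Outcomes; Safety | No grade described; frequency analysed |
| Use of severity | Discussion | Informs the judgement on the larger trial |

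No row connects the load to a prompted symptom or a measurement. Severity appears where the result is used, but not where it would be collected or analysed.

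**2. Size of the administered load** (from the two intervention sections)

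- Fluid: oral 4 + 8 = 12 mL/kg; intravenous 3 + 6 × 1 = 9 mL/kg. Ratio 12/9 = 1.33.
- Salt: oral 0.100 g/kg; intravenous 9 mL/kg × 0.009 g/mL = 0.081 g/kg. Ratio 0.100/0.081 = 1.23.
- Delivery time: oral 1 + 2 = about 3 h; intravenous 1 + 6 = about 7 h.
- At the 110 kg cap: oral 1320 mL and 11.0 g; intravenous 990 mL and 8.91 g.

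These are administered, not absorbed, amounts. They show that the arms differ in load, so a load-related effect could differ by arm. They do not show that it does.

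**3. Would a pilot of this size meet such an event?**

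Assume 25 per arm (50 patients, allocated equally). The chance of at least one event in an arm is 1 − (1 − p)^25. The documents give no value of p, so a range is shown.

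| Assumed true rate p | Calculation | Chance of at least one |
|---|---|---|
| 2% | 1 − 0.98^25 | 40% |
| 5% | 1 − 0.95^25 | 72% |
| 10% | 1 − 0.90^25 | 93% |

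At 5% or more an arm would probably contain a case; at 2% it more likely would not.

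**The case against.** The strongest reply is that the questionnaire and Case Report Form are not shown. Both symptom groups are introduced as examples, and an article condenses a full protocol, so the form may hold further items, a free-text field or a severity column. This stands in part. A reader might infer that the form lists nothing else and that the safety outcome cannot show overload; the text does not establish either. What it does establish is that assessment of all adverse events is tied to a form described by the named symptoms, and none of those is load-related.

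A reader might also infer that the DSMB looks at serious events only. The protocol gives it responsibility for monitoring adverse events generally and lets it recommend stopping on an unexpected event rate; review of serious events is stated in addition. But monitoring depends on what is recorded, and no described route prompts for a non-serious load-related symptom.

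Nor does the protocol say that the heart failure and blood pressure exclusions guard against overload. It gives no reason for them. They are consistent with that concern, and they also remove patients who may be most at risk, which argues for the lower end of the assumed rates.

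Averaging delivery over 3 h and 7 h gives 4.0 against 1.29 mL/kg/h, a ratio of about 3.1. A reader might take this as the difference in physiological load. It is an average administered rate: in the hour before CT the ratio is 4/3 = 1.33, and swallowed salt is not equivalent to infused salt. The protocol itself cites a trial in which 50% more oral salt gave equivalent urinary sodium excretion.

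Finally, this is a feasibility pilot, and the Safety section admits that its comparison is underpowered. That limits what can be concluded, but the same section says the analysis is meant to help design the definitive trial, and it can do so only for events that are recorded.

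**Conclusion.** The point holds as a gap in the safety outcome as the article describes it: no named item and no scheduled blood pressure after dosing captures the effect of the sodium and volume load, and severity is relied on without a described measure. The administered load is 1.33 times higher for fluid and 1.23 times higher for salt in the oral arm, over a shorter time. How often a case would go unprompted depends on an event rate that the documents do not give; at 2% to 10% the chance that an arm of 25 contains at least one runs from 40% to 93%.

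The conclusion assumes that the form follows the Outcomes text. If the full form already has load-related items and a severity grade, the remaining work is to describe them and to report them separately. The primary feasibility outcomes are not affected. This is an inexpensive improvement to a secondary outcome, not a flaw that undermines the pilot.

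**What to change.** - Add load-related items (for example breathlessness, swelling, headache) to the single questionnaire, and ask every item in both arms.
- Add a simple severity grade to every item, so that the severity information named in the Discussion exists.
- In the Safety analysis, report load-related events by arm on a separate line, with their severity, beside the overall frequency.
- Optionally, record blood pressure before the first fluids and at the end of each regimen, and add both readings to Table 1.

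None of this changes treatment. The cost is a few form lines and, if adopted, two blood pressure readings per patient. The protocol states that research personnel are present during oral intake but does not say so for the infusion, so staffing of the last reading in the intravenous arm needs confirming. The downside is a somewhat higher reported adverse event frequency in both arms, because prompted symptoms are reported more often. The separate line keeps that visible.

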### The intravenous saline arm

Patients randomized to this arm will receive IV isotonic (0.9%) saline which is the standard of care recommended by Canadian [19] and international guidelines [8,40-44]. The rate of isotonic saline will be 3 mL/kg given in the one hour before CT and 1 mL/kg/hour for 6 hours post-CT as per Canadian guidelines [19]. Patients weighing more than 110 kg will receive the rate as per a 110 kg patient [18]. The dose will be rounded up to the nearest 5 mL.

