### Study management and patient safety

A trial management group involving the Principal investigator (SH), two Co-investigators (AA, GK) and study coordinator (EM) will review, implement and supervise all aspects of this pilot trial. The Data Management Services group of the Ottawa Hospital Research Institute will generate the random listing. Under the guidance of the Principal investigator and the study coordinator, the coordinating centre located at the Clinical Epidemiology Program of the Ottawa Hospital Research Institute will be responsible for receiving, processing, editing storing and analyzing all data.

A DSMB will have responsibility for the monitoring of adverse events throughout the study and will work independently from the trial. The DSMB will consist of three individuals with expertise in clinical trials, biostatistics, nephrology and radiology. All serious adverse events will be reported to and reviewed by the DSMB. The DSMB will recommend termination or continuation of the study in the event of an unexpected adverse event rate.

All investigational products supplies in the study will be stored in a secure, safe place, under the responsibility of the Investigator.

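### Adverse events are asked about once, at the end of each arm's own regimen (about 2 h post-CT for oral, 6 h for IV), so the safety comparison uses unequal windows and misses delayed non-serious events

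*Protocol article*

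**What the plan says.** All references are to the protocol article.

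- **Outcomes.** Safety is the only secondary outcome. Adverse effects are "assessed by patients self-reported symptoms using a questionnaire with these symptoms listed", and they "will be recorded in a Case Report Form at the end of the volume expansion protocol". The symptoms named are nausea and gastrointestinal symptoms for the oral load. For the saline or its administration they are venipuncture-site problems: "skin irritation and pain, hemorrhage, hematoma, thrombosis, phlebitis".
- **The oral salt and water arm.** "One third of the oral salt and water will be given in 1 hour before the CT and 2/3 in the 2 hours post-CT".
- **The intravenous saline arm.** Saline is given as "3 mL/kg given in the one hour before CT and 1 mL/kg/hour for 6 hours post-CT".
- **Table 1.** The row "Adverse events" has one mark, on Day 1. Creatinine is marked on Day 3 and Day 28, and adherence on Day 1 and Day 28.
- **Safety (statistical analyses).** The overall frequency of adverse events is compared between arms by an unadjusted chi-square or Fisher's exact test. The section says that this outcome is underpowered.
- **Study management and patient safety.** "A DSMB will have responsibility for the monitoring of adverse events throughout the study", and serious adverse events go to that board.

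**The concern.** The recording time is tied to the end of treatment, and treatment lasts longer in one arm than in the other. An intravenous patient is asked about a period more than twice as long as an oral patient is, yet the two frequencies are compared as if they covered the same time.

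The form also closes as the last of the fluid is given. In the oral arm, two thirds of the salt and water is taken in the 2 h just before the questionnaire, so later gastrointestinal symptoms are not recorded. In the intravenous arm, some of the listed events, such as phlebitis, thrombosis and hematoma, can appear after the cannula is out.

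The Discussion says that the trial management group will use the frequency and severity of adverse events to judge whether the benefits of a larger trial outweigh its risks. Numbers from unequal, same-day windows are a weak basis for that judgement. The single Day 1 mark in Table 1 also sits poorly with the DSMB's charge, which runs for the whole study.

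**Working it through.** The article states no adverse event rate, so there is no figure of its own to reproduce. The check adds up the windows and then illustrates what their difference can do.

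**1. Windows, from the two dosing sections**

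| | Oral | IV | IV / oral |
|---|---|---|---|
| Before CT | 1 h | 1 h | |
| After CT, until the form is completed | 2 h | 6 h | 6/2 = 3.0 |
| From start of fluids | 1 + 2 = 3 h | 1 + 6 = 7 h | 7/3 = 2.33 |

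**2. Effect on the comparison, under an assumed equal constant hazard**

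If the IV proportion over 7 h is p, the same hazard over 3 h gives p_oral = 1 − (1 − p)^(3/7). For p = 0.20, 1 − 0.80^(3/7) = 0.091, and 0.091/0.20 = 0.46. The values of p are assumptions that span a range.

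| Assumed IV proportion | Oral proportion, same hazard | Difference (points) | Apparent risk ratio |
|---|---|---|---|
| 10% | 4.4% | 5.6 | 0.44 |
| 20% | 9.1% | 10.9 | 0.46 |
| 30% | 14.2% | 15.8 | 0.47 |
| 40% | 19.7% | 20.3 | 0.49 |

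With one common window, the same hazards give an expected risk ratio of 1.0.

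**3. Chance that the artefact reaches nominal significance**

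The plan is to enrol 50 patients, or about 25 per arm. Taking the proportions above, the two-sided 5% rejection probability of Fisher's exact test was computed exactly, by summing binomial probabilities over all tables. It is about 1.5%, 10%, 17% and 24% for IV proportions of 10%, 20%, 30% and 40%. A normal-approximation calculation gives higher figures, 11% to 35%. Fisher's test is the one the Safety section would use with few events.

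**4. What is and is not observed after Day 1**

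- Symptom questionnaire: not repeated in Table 1 or in the text.
- Serious adverse events: reported to the DSMB.
- Creatinine: 48 h and day 28 in everyone, with repeats every 48 h if raised and again on day 21 if unresolved by day 14 (Data collection).
- Between-arm safety comparison: no section brings later events into it.

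The gap is therefore in delayed non-serious events. Both arms already have contacts at 48 h and day 28 at which the question could be asked.

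**The case against.** **Patients are still followed after Day 1.** This stands. A reader might infer from Table 1 that nothing about safety is seen from Day 2 to Day 28. The article does not support that: serious adverse events and creatinine are followed, and every randomized patient stays in the study to its end, loss to follow-up or death. Only the symptom questionnaire stops on Day 1.

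**The direction of the bias is not fixed.** This stands too. A reader might infer that the design favours the oral arm by construction. Shorter observation does so if hazards are equal, and so do missed late gastrointestinal symptoms. But late cannula-site events are attributed to the intravenous technique, and missing them favours that arm.

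**The constant-hazard model fits poorly.** Largely right. The listed events differ by arm, and many follow a discrete act (cannulation, swallowing capsules) rather than accruing hour by hour. The calculation shows what unequal windows can do; it does not estimate what they will do.

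**A longer infusion is part of the intravenous strategy, so its symptoms are real.** That is a fair reading of a tolerability comparison. It justifies counting symptoms that arise during hours 2 to 6 post-CT in the intravenous arm. It does not justify leaving the same hours unobserved in the oral arm.

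**The outcome is admitted to be underpowered, and this is a pilot.** That caveat concerns precision and does not remove bias. It does limit the consequence: no primary or efficacy conclusion depends on this comparison.

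**Table 1 is condensed, and the full protocol may add later inquiry.** The table is incomplete elsewhere; for example, it does not show the conditional creatinine repeats. But the recording time does not rest on the table, because the Outcomes text states it directly for all adverse events.

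**Conclusion.** The point holds for the questionnaire-based safety comparison. As written, it compares adverse event frequencies over 3 h against 7 h from the start of fluids (2 h against 6 h post-CT) and leaves out delayed non-serious events in both arms. The windows follow directly from the article and need no assumption.

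The size of the resulting bias cannot be derived from the article, and its net direction is uncertain. The apparent risk ratio of 0.44 to 0.49 depends on an equal constant hazard and on assumed intravenous proportions of 10% to 40%. On the same assumptions, Fisher's exact test would report a difference in about 1.5% to 24% of such trials.

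Severity is moderate. It should be fixed because safety is the only secondary outcome and informs the decision on a larger trial. It does not threaten the feasibility outcomes, and the documents do not support calling it critical.

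**What to change.** - Give the same questionnaire to both arms at one common time counted from the CT, at or after 6 h post-CT. Use the same mode in both arms: if oral patients have gone home and are telephoned, telephone the intravenous patients as well.
- Repeat it in both arms at the existing 48 h and day 28 creatinine contacts.
- State in the Safety section that arms are compared only over these common windows. Any record kept at the end of each regimen can be reported by arm as a description of tolerability.
- Add the new marks to Table 1, so that it agrees with the DSMB's responsibility for the whole study.

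The cost is one extra contact on Day 1, a few added questions at visits already planned, and a change to the case report form. No dose or treatment schedule is affected. As recruitment began in October 2014, patients already assessed under the current text should be identified and reported separately for this outcome.
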